### Data management

Web-based data from the study sites will be submitted to the data management site or central site (Siriraj Hospital, Mahidol University, Bangkok, Thailand). Patients will be assigned a unique identification number. Any data that are transferred to the data management site will be anonymized for to protect personal identification information and confidentiality. Investigators at the data management site can review the data, verify data, and send queries to the study site for clarification. Site monitoring will be performed at every site to assess the data quality and to ensure that the study is conducted in accordance with Good Clinical Practice guidelines.

### Statistical analysis

Data analysis will be performed at the central site. Continuous variables with normal distribution will be presented as mean ± SD, and continuous variables with non-normal distribution will be presented as median and IQR. Categorical variables will be presented as absolute numbers and percentages. All statistical tests will be 2-tailed, and *P <* 0.05 will be regarded as significant. Moreover, if necessary, post hoc analyses will be conducted. The baseline characteristics of patients will be presented as mean ± SD, and frequency for continuous and categorical variables, respectively. The incidence rates of each clinical outcome will be presented as rates per 100 person-years with a Poisson 95% CI and a 2-sided *P* value. Univariable and multivariable analysis will be performed to identify factors that predict adverse clinical outcomes using the Cox proportional Hazard model. HRs and 95% CIs will be reported. The selection of variables in multivariable model will be based on the prior knowledge of the covariates that might impact the outcome and theory driven approaches that might be the predictors of each clinical outcome in combination with the results of the univariate analysis. Multivariable analysis using backward elimination with a *P* value <0.05 as the stopping criterion will be used. The association of the pattern of antithrombotic use and clinical outcome will be analyzed using the Cox model. For the warfarin group, the time in the therapeutic range (TTR) will be calculated using the Rosendaal method,^22^ The analysis related to warfarin will be performed with and without consideration of the TTR data.

#### Model development

We will follow the Transparent Reporting of a multivariable prediction model for Individual Prognosis or Diagnosis reporting guideline for the prediction model.^23^ The risk prediction model for the clinical outcomes of interest will be developed from the variables derived from the multivariable model. The probability of outcome at time A for each patient will be calculated by using the following equation, which is derived from Cox proportional hazards model:$$P_{\text{Outcome}}\;\text{at}\;\text{time}\;A=1\;–\;S_{0}{\left(t\right)}^{\exp\left(\text{Prognostic}\;\text{Index}\right)}$$

where S_0_(t) is the average survival probability at time t (ie, at time A), and prognostic index is the sum of the predictor products and the coefficients obtained from the multivariable model.

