#### Model validation

Model applicability assessment will be performed according to the Prediction model Risk Of Bias ASsessment Tool suggestions.^24^ Bootstrapping based on 100 to 1,000 bootstrap samples will be used to verify the fitted model. Calibration will be tested using the calibration slope based on the observed and predicted hazards of the outcome.^25^ The Harrell C-statistics will be used to measure model discrimination. C-statistics vary from 0 to 1, and a value close to 1 reflects a good prediction model.^26^ Receiver-operating characteristics curve will be used to calculate the area under curve and to compare C-statistics. The D-statistic assesses the discrimination ability of the fitted model for low- and high-risk patients.^26^ C- and D- statistics will also be calculated after the bootstrapping as an internal validation. The Brier score will be evaluated to assess the predictive ability of the model.^27^ Net reclassification index and integrated discrimination index will be calculated based on previously proposed methods to determine the influence of the predictive model on the reclassification of the study subjects.^28^ Decision-curve analysis will be used to estimate the clinical usefulness of the prediction models by assessing the ability to make better decisions with a model than without it.^29^

All statistics were performed using the SPSS statistical software version 18.0 (SPSS, Inc) and R version 3.6.3 (R Foundation for Statistical Computing).

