### Sample size calculation

The sample size calculation for the predictive model development was based on the 10 events per variable concept, which suggested that we need at least 10 events per candidate variable.^30^ The results from COOL-AF phase 1 indicated that the number of candidate variables for death, SSE, and major bleeding is approximately 10. Using the rate of death, SSE, and major bleeding from COOL-AF phase 1,^3^ the number of patients needed for predictive model development was highest at 3,334 for SSE. If the rate of incomplete or loss follow-up is 10%, the sample size needed was 3,667. This sample size also covers the sample size needed to determine the rate of clinical outcomes (death, SSE, and major bleeding).

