## Discussion

The COOL-AF registry Phase 1 study received funding from the Health System Research Institute (HSRI) and the Heart Association of Thailand under the Royal Patronage. It is a prospective cohort study that enrolled 3,461 AF patients from 27 hospitals across Thailand. The enrollment period spanned from 2014 to 2017, and the participants were scheduled for follow-up visits every 6 months for up 3 years.^5^ The findings from the COOL-AF Phase 1 study have provided valuable insights into the use of anticoagulant medications and various aspects of managing AF patients in Thailand. Key findings from COOL-AF Phase 1 are summarized in Table 5.

**Table 5 tbl5:** Key Findings From COOL-AF Phase 1

1. Thai AF patients had high risk of bleeding events including ICH^3^ 2. Even though the majority of patients received warfarin, the benefit of warfarin will be only in patients with good TTR (TTR >65%)^42^ 3. In patients with poor TTR (majority), giving warfarin had a negative net clinical benefit (benefit in stroke prevention less than risk of major bleeding) compared with not giving OAC at all (under submission) 4. Target INR of Thai AF patients is different from the international recommended INR. In patients with age <70 years, the target INR is 2.0-3.0, whereas in those age 70 years, the target INR was 1.5-3.0^43^ 5. DOAC is better than warfarin in Thai AF^44^^,^^45^ 6. Promotion of anticoagulation clinic is important to improve quality of warfarin use 7. Non-CV death is as important as CV death in AF patients^46^ 8. Promotion of holistic care of AF patients is essential to improve outcomes (appropriate OAC use, appropriate treatment of symptoms and comorbidities)^45^^,^^47^

CV = cardiovascular; other abbreviations as in Tables 1, 3, and 4.

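### The Cox formula for individual risk suits all-cause death, but for SSE and major bleeding it gives the risk if nobody died and so over-predicts, modestly on average and more where mortality is high

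*Protocol article*

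**What the plan says.** The Statistical analysis section plans univariable and multivariable work to "identify factors that predict adverse clinical outcomes using the Cox proportional Hazard model". Model development then turns that model into an individual risk: "The probability of outcome at time A for each patient will be calculated by using the following equation", which the article says comes from the Cox model, with the equation 1 − S0(t)^exp(PI). S0(t) is described only as an average survival probability at the chosen time. No separate rule is given for outcomes other than death.

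The Sample size section shows which outcomes this covers: "the number of candidate variables for death, SSE, and major bleeding is approximately 10". SSE and major bleeding are therefore modelled as outcomes in their own right, separate from death.

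Model validation adds a Brier score, and states that "Decision-curve analysis will be used to estimate the clinical usefulness of the prediction models". Its calibration measure is a slope comparing observed with predicted hazards. Competing risks, cumulative incidence and a subdistribution model are not mentioned anywhere in the article.

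On mortality, Table 5 in the Discussion lists as a Phase 1 finding that "Non-CV death is as important as CV death in AF patients", and the registry comparison describes mortality in AF as high. Neither gives a rate. Table 2 excludes patients whose other diseases give a life expectancy under 3 years.

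**The concern.** For all-cause death nothing competes, and one minus the Cox survival function is the probability of the event. For SSE or major bleeding, a patient who dies first can no longer have the event. A single-event Cox survival function can only handle that death as censoring, so the equation returns the risk in a population where death has been abolished. The article nevertheless calls the result each patient's probability.

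Prediction models are a primary objective, and absolute risk is what a user would read from them. The Brier score and decision-curve analysis are computed from these absolute risks. The relative error depends almost entirely on the patient's death rate, so it differs between patients and one average recalibration cannot remove it. The one named calibration check cannot reveal it either: the cause-specific hazards may be estimated correctly while their conversion to risk is wrong.

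**Working it through.** **The plan's own figure first.** The Sample size section says that "we need at least 10 events per candidate variable" and takes about 10 candidate variables, hence 10 × 10 = 100 events. The stated 3,334 implies an SSE proportion of 100/3,334 = 3.0%; this is back-calculated, as the rate and its time frame are not printed. 100/0.03 = 3,333.3, rounded up to 3,334, and 3,334 × 1.10 = 3,667.4, which matches the stated 3,667. The sample size reproduces and does not depend on the present point.

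**Inputs for the check.**
- Horizon t = 3 years, from the 36-month follow-up.
- Event hazard λ: assumed. The value 1%/year gives about 3% over 3 years, in line with the implied proportion if that is a 3-year figure.
- Hazard μ of death without a prior event: assumed, because the article gives no death rate.
- Constant hazards: assumed.

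**Formulas.**
- Plan's equation with death censored: 1 − exp(−λt)
- Actual probability (cumulative incidence): λ/(λ+μ) × [1 − exp(−(λ+μ)t)]

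**Worked case, λ = 0.01, μ = 0.03.** Plan: 1 − exp(−0.03) = 2.96%. Actual: 0.01/0.04 × [1 − exp(−0.12)] = 0.25 × 0.1131 = 2.83%. Ratio 1.045.

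| λ per year | μ per year | Plan's formula | Cumulative incidence | Excess (points) | Relative excess |
|---|---|---|---|---|---|
| 0.01 | 0.03 | 2.96% | 2.83% | 0.13 | 4.5% |
| 0.01 | 0.05 | 2.96% | 2.75% | 0.21 | 7.6% |
| 0.03 | 0.10 | 8.61% | 7.45% | 1.15 | 15.5% |
| 0.03 | 0.20 | 8.61% | 6.50% | 2.11 | 32.4% |

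**Dependence on the death rate.** With the formula risk set at 3.00%, the ratio of formula to cumulative incidence is 1.03 at 2 deaths per 100 person-years, 1.06 at 4, 1.11 at 7, 1.16 at 10, 1.24 at 15 and 1.33 at 20. With an event rate of 5 per 100 person-years the ratios at 4, 10 and 20 are 1.06, 1.15 and 1.32. So the relative excess hardly changes with the event rate and is driven by mortality.

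**Scale against sampling error.** For a 3% risk in 3,334 patients the 95% half-width is 1.96 × √(0.03 × 0.97/3,334) = 0.58 points. The first two rows of the table are 0.13/0.58 = 0.22 and 0.21/0.58 = 0.36 of that.

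**The case against.** The case on the other side has several parts.

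- **Censoring is not written down.** The article never says that death is censored. The form 1 − S0(t)^exp(PI) is also how a subdistribution-hazards model yields cumulative incidence, and a condensed article may leave competing-event rules to the full protocol or SAP. The first part stands: censoring at death is implied, not stated. But the article says the equation comes from a Cox proportional hazards model, which does not support the subdistribution reading. It prints the equation and calls its result a probability, so this is a stated rule and not an omitted detail. An analysis plan that used cumulative incidence for SSE and bleeding would contradict it.
- **The average effect is small.** This stands. On the base case it is 0.13–0.21 points, roughly a fifth to a third of the sampling half-width. It is, however, systematic.
- **The large figures are hypothetical.** This stands. At 20% per year, 1 − exp(−0.6) = 45% of the group would die within 3 years, and the life-expectancy exclusion makes such patients less common. It does not remove them, because it covers only limited survival from other diseases.
- **Not every death competes.** This stands. Deaths after a first event do not compete, and a fatal bleed is itself a bleeding outcome. The μ above is event-free death; using all-cause mortality in its place would overstate the bias.

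A reader might also infer that the oldest and sickest patients will be over-predicted by up to a third, or that treatment decisions will change. The documents support neither. They give no death rate by age or comorbidity and no decision threshold, and the Table 5 finding compares causes of death without giving a rate. Nor should calibration be counted among the absolute-risk outputs that carry the error, since the planned slope is on hazards.

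**Conclusion.** The point holds. Followed as written, the plan over-predicts the absolute risk of SSE and major bleeding at any death rate above zero. The direction follows from the equation once death is censored, which a single-event Cox model implies.

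The size rests on assumed constant hazards and assumed event-free death rates over 3 years. It is modest on average, and larger only where mortality is high: about 15.5–32% relative in a hypothetical group with 10–20% mortality per year.

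Only the conversion to absolute risk for these two outcomes is affected, together with the Brier score and decision curve built on it. Cause-specific hazard ratios for predictors, rates per 100 person-years, the sample size and the all-cause death model remain sound. The change should be made before the models are fitted; the point does not threaten the study.

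**What to change.** Restrict the Model development equation to all-cause death. For SSE and major bleeding:

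1. Predict cumulative incidence with death as a competing event, either by combining cause-specific Cox models for the event and for event-free death, or by a Fine-Gray model. State which one, and say that a fatal bleed counts as a bleeding event and not as a competing death.
2. Add calibration of predicted risk against observed risk from the Aalen-Johansen estimator, alongside the planned slope on hazards.
3. Use competing-risk versions of the Brier score and decision curve.
4. Keep the cause-specific Cox hazard ratios for the predictor analysis.

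The cost is a few sentences in the analysis plan, standard R code, and slightly more complex analysis and reporting. R is already planned, and deaths and their causes are already collected. Data collection and sample size do not change, and the last follow-up is not expected until June 2029.

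### The risk equation defines its two terms incompatibly: an average survival probability is paired with an uncentred prognostic index, so absolute risks computed literally are off by a constant hazard factor of unknown direction

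*Protocol article*

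**What the plan says.** In the Protocol article, Statistical analysis, Model development, the outcome probability at a chosen time is 1 − S0(t)^exp(prognostic index), an equation "which is derived from Cox proportional hazards model". The terms are then defined: S0(t) "is the average survival probability at time t (ie, at time A), and prognostic index is the sum of the predictor products". Each product multiplies a predictor by its fitted coefficient. No centring of the index is mentioned.

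Under Model validation the article states: "Calibration will be tested using the calibration slope based on the observed and predicted hazards of the outcome". The slope is the only calibration measure named, and its scale (hazard or log hazard) is not given. Harrell's C and the D-statistic are planned for discrimination. Two further measures depend on absolute risk: "The Brier score will be evaluated to assess the predictive ability of the model", and "Decision-curve analysis will be used to estimate the clinical usefulness of the prediction models".

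**The concern.** The equation has two correct forms. One uses survival for a patient whose predictors are all at zero or reference, with the plain sum of coefficient × predictor. The other uses survival at the mean predictors, with that sum minus its mean. The article takes the survival term from something like the second form and the index from the first.

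Developing prediction models is a primary objective, and the sample size is built on it. If the definitions were followed as printed, the ranking of patients would be right but the risk quoted to each of them would be wrong, unless the constant happened to equal 1. The Brier score and decision curve would be computed from those wrong risks.

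**Working it through.** **Inputs.** The equation and its definitions come from Model development. The article gives no predicted risk to reproduce, and no coefficients, coding or predictor means; these are assumed below. An illustrative risk level comes from Sample size calculation: "we need at least 10 events per candidate variable", and "the number of candidate variables for death, SSE, and major bleeding is approximately 10". That gives 10 × 10 = 100 events, and 100 / 3,334 = 3.0% for SSE, so survival is about 0.97. No time horizon is attached to this figure.

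**Step 1: algebra.** Let H0 = −ln S0(t) at PI = 0, b the coefficients and x̄ the mean predictors.
- Correct cumulative hazard for a patient with predictors x: H0 × exp(b′x).
- If average means survival at mean covariates, the cumulative hazard put into the equation is H0 × exp(b′x̄). With an uncentred PI the result is H0 × exp(b′x̄) × exp(b′x). Every patient's hazard is multiplied by exp(mean PI).
- If average means the cohort (Kaplan-Meier) survival S_KM, the multiplier is −ln(S_KM) / H0, a different constant.

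**Step 2: size for the average patient.** Take survival at mean covariates as 0.97, so the correct risk is 3.0%. The printed pair gives 1 − 0.97^exp(m) for mean PI m:
- m = −0.5: 1 − 0.97^0.607 = 1.8%
- m = 0.5: 1 − 0.97^1.649 = 4.9%
- m = 1: 1 − 0.97^2.718 = 7.9%
- m = 2: 1 − 0.97^7.389 = 20.2%

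**Step 3: simulation.** 20,000 patients, risk about 3%, Cox fit with Breslow baseline, and four assumed predictor sets:
- (a) five binary risk factors, prevalence 17% to 70%, hazard ratios 1.2 to 2.0;
- (b) the same plus age in years (mean 68, log hazard ratio 0.03 per year);
- (c) a protective anticoagulant term (75% use, hazard ratio 0.5) plus prior stroke;
- (d) a haemoglobin-type predictor (mean 13, coefficient −0.12 per unit) plus the binary factors.

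Survival at mean covariates with uncentred PI:

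| Set | exp(mean PI) | Mean predicted | Observed | O/E | Slope of observed on predicted hazard, by decile | Brier, mismatched vs matched |
|---|---|---|---|---|---|---|
| a | 1.94 | 5.9% | 3.1% | 0.52 | 0.52 | 0.0307 vs 0.0297 |
| b | 12.2 | 29.5% | 3.0% | 0.10 | 0.09 | 0.1112 vs 0.0286 |
| c | 0.66 | 2.0% | 3.0% | 1.51 | 1.54 | 0.0287 vs 0.0285 |
| d | 0.41 | 1.3% | 3.1% | 2.41 | 2.48 | 0.0305 vs 0.0301 |

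- With either matched pair, O/E was 1.000 in all four sets.
- With Kaplan-Meier survival and uncentred PI, the multipliers were 2.11, 13.9, 0.72 and 0.46.
- With Kaplan-Meier survival and a centred PI, O/E was still 0.88 to 0.92, so centring alone does not repair that reading.

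**Step 4: what the planned measures would show.** The C- and D-statistics depend on the ordering of patients, which a constant multiplier leaves alone. The calibration slope on the log-hazard/PI scale was 1.000 in every mismatched case. The slope on untransformed hazards moved away from its matched value of about 1.01 to 1.04. The Brier score changed clearly only in set b.

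**The case against.** The strongest reply is that S0(t) in a Cox risk equation ordinarily denotes baseline survival at PI = 0, and on that reading the equation is correct as printed. The word average would then be a slip of description. This stands as far as it goes: the article does not prove that the analysts will compute wrong risks. It does not rescue the text, because the definition given is a different quantity and nothing elsewhere in the article corrects it.

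A reader might infer two stronger claims that the article does not support. The first is that predicted risks will be too high. Direction depends on coefficients and coding that are not given; with protective terms, as in sets c and d, risks come out too low. Such terms are plausible here, since antithrombotic pattern and its effect on outcomes is itself an objective. The second is that the planned calibration slope cannot detect the error. That holds on the log-hazard/PI scale. The article speaks of observed and predicted hazards without fixing the scale, and a slope on untransformed hazards would shift. The Brier score and decision curve would also respond, although none of these isolates the cause.

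It is also fair to say that an article may leave calibration-in-the-large and calibration plots to the analysis plan, and that this one commits to recognised reporting and risk-of-bias guidance for prediction models. Their absence is therefore not part of the finding; the observed/expected ratio is offered below only as a check.

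**Conclusion.** Wrong as written, of moderate severity. The two definitions cannot both be used in the printed equation. Taken literally they multiply every predicted cumulative hazard by a constant: exp(mean PI) if average means survival at mean covariates, another constant if it means cohort survival. In the illustrations the average patient's risk ranges from 1.8% to 20.2% against a correct 3.0%. These sizes rest on assumed mean PIs from −0.5 to 2 and on a 3.0% risk back-calculated from the sample size with no stated horizon, so they show scale and do not forecast what this study will report. Severity is held at moderate because the proven fault is in the written definition and can be corrected before any model is fitted. The recruitment target, data collection, hazard ratios, variable selection and discrimination measures are unaffected.

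**What to change.** State one matched pair in the protocol or analysis plan:
- S0(t) is baseline survival with all predictors at zero or reference, and PI stays uncentred; or
- the survival term is survival at the mean predictors, and the exponent is exp(PI − mean PI). Cohort-average survival should not be used here, because it stays slightly off even with a centred PI.

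Report S0(t) at the prediction horizon and, if PI is centred, the mean PI, so that others can apply the model.

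As an inexpensive check, report calibration-in-the-large (observed/expected risk at the horizon) next to the slope, and say on which scale the slope is fitted. The cost is one line of definition and one or two extra lines of output. No change to design, sample size or data collection is needed.

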#### Model validation

Model applicability assessment will be performed according to the Prediction model Risk Of Bias ASsessment Tool suggestions.^24^ Bootstrapping based on 100 to 1,000 bootstrap samples will be used to verify the fitted model. Calibration will be tested using the calibration slope based on the observed and predicted hazards of the outcome.^25^ The Harrell C-statistics will be used to measure model discrimination. C-statistics vary from 0 to 1, and a value close to 1 reflects a good prediction model.^26^ Receiver-operating characteristics curve will be used to calculate the area under curve and to compare C-statistics. The D-statistic assesses the discrimination ability of the fitted model for low- and high-risk patients.^26^ C- and D- statistics will also be calculated after the bootstrapping as an internal validation. The Brier score will be evaluated to assess the predictive ability of the model.^27^ Net reclassification index and integrated discrimination index will be calculated based on previously proposed methods to determine the influence of the predictive model on the reclassification of the study subjects.^28^ Decision-curve analysis will be used to estimate the clinical usefulness of the prediction models by assessing the ability to make better decisions with a model than without it.^29^

All statistics were performed using the SPSS statistical software version 18.0 (SPSS, Inc) and R version 3.6.3 (R Foundation for Statistical Computing).

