### Study protocol

After the consent process, investigators will record the required data from medical records and patient interviews. Patient data will be recorded in the web-based system that was created to be user-friendly for data entry. After the data entry is completed, the site investigators will submit the data.

Follow-up visit data will be recorded at 6, 12, 18, 24, 30, and 36 months after enrollment. The follow-up data will be recorded in a similar manner. The window period of data recording will be 1 month. Email reminders will be sent out to site investigators every 2 weeks to remind them of any overdue of the data entry or the incomplete record. The timeline of the study is shown in Figure 2.

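### An ROC curve is assigned to compare Harrell C-statistics of censored Cox models, and ROC area and Brier score are planned without a fixed prediction time

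*Protocol article*

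**What the plan says.** In the protocol article, Model development derives an absolute risk from the Cox model: "The probability of outcome at time A for each patient will be calculated by using the following equation". Time A is given no value there or elsewhere in the article.

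Model validation names the discrimination measure: "The Harrell C-statistics will be used to measure model discrimination". It then gives the ROC curve two tasks: "Receiver-operating characteristics curve will be used to calculate the area under curve and to compare C-statistics". It also plans an overall accuracy measure: "The Brier score will be evaluated to assess the predictive ability of the model". Calibration is assessed on the hazard scale ("Calibration will be tested using the calibration slope based on the observed and predicted hazards of the outcome"), and a D-statistic and bootstrap validation are planned.

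Censoring is expected. Sample size calculation states: "If the rate of incomplete or loss follow-up is 10%, the sample size needed was 3,667". Study protocol sets the visit schedule: "Follow-up visit data will be recorded at 6, 12, 18, 24, 30, and 36 months after enrollment". Trial status puts the last recruitment in June 2026 and the last visit in June 2029. The Abstract (Results) plans a report when enrollment is complete and one year of follow-up is available.

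**The concern.** Two things are fixed badly in the text.

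First, the comparison does not match the measure. Harrell C looks at pairs of patients in which the shorter time ends in an event and asks whether that patient had the higher predicted risk. An ROC area at a fixed time sets patients with the event by then against patients without it. An analyst who follows the sentence would report a test on one quantity as if it were a test on the other.

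Second, an ROC area and a Brier score both require a known yes/no status at a stated time. With time A open and patients lost before it, some statuses are unknown and the article does not say how they enter. Developing prediction models is a primary objective and sets the sample size, so the measures used to judge and choose between models deserve an exact definition.

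**Working it through.** **1. The plan's own figures.** Ten events for each of about 10 candidate variables gives 10 × 10 = 100 events. The 3,334 patients stated for SSE then imply 100 / 3,334 = 3.0% with an event. Adding 10%: 3,334 × 1.10 = 3,667.4, which matches the stated 3,667. (Dividing instead, 3,334 / 0.90, gives 3,705, about 1% more. Nothing here turns on that.) The figure needed below is the 10% loss.

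**2. The two measures side by side.**
- Patients with events at months 6 and 30: Harrell C uses the pair. A 36-month ROC area does not, because both are cases.
- One patient with an event at month 12, another lost event-free at month 18: Harrell C uses the pair. A 36-month ROC area can use it only if a status is assigned to the lost patient, or if weights handle the loss.

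The two areas therefore rest on different pairs, and a difference in one is not a difference in the other.

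**3. Follow-up available.** Final analysis: June 2026 to June 2029 is 36 months, so the last patient enrolled can also reach month 36. Report one year after last enrollment (about June 2027): follow-up runs from 12 months for the last patient to 36 months for the first.

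**4. Size if observed status were used.** The article gives no AUC, Brier score or 36-month risk, so these inputs are assumptions: exponential event times; one normal prognostic index with log hazard ratio 0.9 per SD; 36-month risks of 3%, 9% and 20%; no competing death; correct predicted risks; 1,000,000 simulated patients per setting. Loss was either 10% at random, uniform over 36 months, or more likely at higher risk (7.5-8.9% censored before an event). At the early report, follow-up was uniform from 1 to 3 years, with 10% random loss in addition.

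Brier score = mean of (status − predicted risk)². The naive version sets status to 1 only for an observed event, so a lost patient counts as 0. The true version uses actual status at 36 months. Shortfall = 1 − naive / true.

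| Setting | Risk | ROC area, true / naive | Brier, true / naive | Brier shortfall |
|---|---|---|---|---|
| Random loss | 3% | 0.7406 / 0.7406 | 0.02842 / 0.02716 | 4.4% |
| | 9% | 0.7426 / 0.7416 | 0.07523 / 0.07230 | 3.9% |
| | 20% | 0.7529 / 0.7509 | 0.13569 / 0.13217 | 2.6% |
| Risk-related loss | 3% | 0.7389 / 0.7276 | 0.02813 / 0.02624 | 6.7% |
| | 9% | 0.7439 / 0.7315 | 0.07493 / 0.07160 | 4.4% |
| | 20% | 0.7528 / 0.7391 | 0.13547 / 0.13354 | 1.4% |
| Early report, 36-month horizon | 3% | 0.7389 / 0.7363 | 0.02812 / 0.01886 | 32.9% |
| | 9% | 0.7432 / 0.7406 | 0.07520 / 0.05458 | 27.4% |
| | 20% | 0.7526 / 0.7449 | 0.13557 / 0.11043 | 18.5% |

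**5. What censoring weights do.** The weights were 1/G(event time) for observed events, 1/G(36 months) for patients known event-free at 36 months, and 0 for those lost earlier, with G the Kaplan-Meier estimate of remaining uncensored.
- Random loss: the weighted ROC areas equal the true ones to four decimals. The weighted Brier scores are 0.02849, 0.07521 and 0.13574, close to the true values.
- Risk-related loss: these covariate-free weights do not suffice. The weighted ROC areas are 0.7457, 0.7501 and 0.7584, which is 0.006 to 0.007 too high.
- Early report at 36 months: no simulated patient is known event-free at 36 months, so the weighted ROC area cannot be computed. The weighted Brier scores (0.02647, 0.06457, 0.09964) still miss the true values. Weights cannot rescue a horizon that the follow-up does not reach.

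**The case against.** The strongest reply is that this is a journal article. Estimator details are commonly left to the full protocol or analysis plan, the Brier score carries a citation, and R can produce censoring-adjusted versions. A time-dependent ROC curve and a weighted Brier score would both satisfy the sentences as printed. The main measures (Harrell C, the D-statistic and the hazard-based calibration slope) already accommodate censoring. With 10% random loss the effect is small even under the worst coding.

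Most of this stands, and it rules out several stronger readings:
- A reader might infer that the plan uses uncensored versions and counts lost patients as event-free. The text does not say so.
- A reader might infer that validation of the Phase 1 models rests on these figures. The article lists that validation as a secondary objective and does not tie it to ROC area or Brier score.
- A reader might take the 19-33% Brier error as the expected error. It needs a 36-month horizon at the early report, which the article does not state. A 12-month horizon there would involve no administrative censoring.
- How death is handled as a competing event for SSE and bleeding is a separate question.

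The reply does not cover the ROC sentence itself. That sentence is a stated method given a task it does not perform, and a later document that followed it would carry the mismatch forward.

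**Conclusion.** The point holds in a limited form. The stated comparison is mismatched: an ROC comparison does not test a difference in Harrell C. This needs no simulation and no assumption about coding. The ROC area and Brier score also lack a horizon, because time A is unspecified, and no censoring-adjusted form is given.

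The numerical consequence is conditional on observed status being used at 36 months. At full follow-up with about 10% random loss, the Brier score is about 3-4% too low and the ROC area changes by at most 0.002. If loss depends on risk, the ROC area is 0.011-0.014 too low and the Brier score 1-7% too low. Only a 36-month horizon at the report one year after last enrollment gives a large distortion: Brier roughly 19-33% too low, ROC area 0.003-0.008 too low. All these sizes rest on the assumed risks, index strength and loss patterns. The documents do not show that model performance will be misstated. The correction is still worth making, because it concerns a primary objective and is cheap.

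**What to change.** - Replace the ROC sentence. Compare models by the bootstrap difference, with confidence interval, in Harrell C, or in time-dependent AUC if that is preferred, using the same measure for both models. Bootstrapping with 100 to 1,000 samples is already planned; use the upper end for the interval.
- Fix time A separately for each report, at a horizon that the follow-up then supports: for example, 12 months at the report one year after last enrollment and 36 months at the final analysis.
- Compute AUC and Brier score at that time with inverse-probability-of-censoring weights. Let the weights depend on the predictors, since weights without covariates do not correct risk-related loss.

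The cost is a few sentences in the analysis plan and standard R code. No extra data or patients are needed.
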